### **1.7 Risk minimisation plan:**

The sham treatment in the control arm is not harmful to the patient: no disc injection, no placebo injection will be performed in the control patients. The patients with IDD are chronic patients, painful but with no vital risk or no significant risk of delaying effective therapy. The 6 months follow up with conventional therapy is not a reduction of chance to IDD cure as it is a slow irreversible disc degeneration.. Conventional treatment as physiotherapy or analgesic is allowed during the trial period (NSAID and opioid as suggested by “standard of care” [Cartabellotta et al., 2017]). In case patients became painful and who develop “peripheral neurological deficit” they will undergo electromyography of the legs. In case the results obtained show pinched sciatic nerve, the investigator will decide to exclude the patients from

clinical trial and shift the patient to the appropriate standard of care (NSAID, steroid injection, rest, physiotherapy)[Cartabellotta et al., 2017]. In case of severe neuropathic pain (sciatica), the patient will be allowed to perform surgery, he will be considered as a failure. We enclose adequate risk minimization measures in the protocol avoiding the inclusion of patients who are not eligible to the intravertebral disc surgery or so painful that they have high probability to undergo surgery in the next 6 months period as well as patients with herniated discs.

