### 3.2 Exclusion criteria

- Congenital or acquired diseases leading to spine deformations that may upset cell application (scoliosis, isthmus lesion, sacralization and hemisacralization, degenerative spondylolisthesis).
- Spinal segmental instability assessed by dynamic X-Ray.
- Symptomatic facet joints syndrome on MRI (facet joints hyperintensity and hypertrophy evaluated at coronal T2 weighted MRI).
- Prior to the screening visit, has received:
  - Oral corticosteroid therapy within the previous 3 months, OR
  - Intramuscular, intravenous or epidural corticosteroid therapy within the previous 3 months
- Presence of a 4th level with symptomatic IDD (modified Pfirrmann score 3-4, Griffith score 3-7) in the lumbar spine.
- Spinal canal stenosis (Schizas score > B).
- History of spinal infection.
- Lumbar disc herniation and sciatica.
- Endplate abnormality such as Schmorl's Nodes.
- Previous discal puncture or previous spine surgery.
- IDD with Modic II and III changes on MRI images.
- Patients not eligible to the intravertebral disc surgery.
- Patients who have the risk to undergo a surgery in the next 6 months.
- Patients with local infusion device/devices for corticosteroids.
- Obesity with body mass index (BMI in Kg/size in m^2) greater than 35 (obesity grade II).

- Participation in another clinical trial or treatment with another investigational product within 30 days prior to inclusion in the study.
- Abnormal blood tests: hepatic (alanine aminotransferase [ALT] and/or aspartate aminotransferase [AST]  $>1.5 \times$  upper limit of normal [ULN]), renal, pancreatic or biliary disease, blood coagulation disorders, anemia or platelet count of  $<100 \times 10^9/L$ .
- Pregnant or lactating women, or premenopausal women not using an acceptable form of birth control, are ineligible for inclusion. Contraception will be maintained during treatment and until the end of relevant systemic exposure. Additional pregnancy testing will be performed at the end of relevant systemic exposure. The patients will be required to use contraception from initial treatment administration until 24 months after the last dose of study drug.

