### **3.5 Withdrawal of the clinical trial**

Patients may always and without specification of reasons withdraw their informed consent and, as a corollary, withdraw from the trial related therapy or the entire clinical trial. The investigator also has the right to withdraw patients in agreement with the sponsor or his delegate.

Patients must be withdrawn from the study under the following circumstances:

- The patient withdraws consent,
- Loss of contact to the patient after 3 reminders,
- Development of an intercurrent illness or condition, which would interfere with the patients continued participation,
- Occurrence of a SAE or an exclusion criteria, which would interfere with the patients continued participation,

Discovery that the subject entered the clinical trial in violation of the protocol or occurrence of a significant protocol violation during the clinical trial. The withdrawal will be decided after notice of the principal investigator and methodologist.

Other reason in the opinion of the investigator that cells should not be injected to prevent the patient from harm.

Any situation that in the opinion of the investigator would pose unacceptable risks to the patient if trial participation is continued.

For any discontinuation the investigator should obtain all required details and should document the date and reason of the premature termination in the CRF.

If the reason for withdrawal is an AE, the specific event will be recorded in the eCRF. The investigator will make thorough efforts to document the outcome.

If a patient is withdrawn from the clinical trial before injection of the cells, it will be replaced by another eligible patient.

If a pregnancy occurs, the patient will be withdrawn from the clinical trial and will be closely followed up.

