### **5.6 Application of sham procedure**

In the other group, the sham procedure will be performed in the same conditions in order to keep blind the patient. The person in charge of injection, who's the only unblinded investigator will mimic intradiscal injection by using imaging with only paravertebral muscle puncture. No disc injection, no placebo injection will be performed in the control patients.

The annulus will not be perforated. A puncture with a needle into deep muscle (Musculus erector spinae) will be performed, however no lidocaine or other fluids will be delivered in the vicinity of the disk, as to avoid any positive or negative bias. As the patient will be lying on the table and covered by the drape, he/she will not be aware that the C-arm is not in action during the procedure.

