### **7.5 Handling of dropouts or missing data**

Rules for imputation of missing data will be detailed in the SAP. When analyzing efficacy data, if the missing data is type MAR (Missing At Random) or MCAR (Missing Completely At Random), a multiple imputation will be implemented.

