### Expected Adverse Reaction related to injection of autologous bone marrow mesenchymal cell (undetermined frequency, not severe except for immunological reaction)

- transient lumbar pain
- elevation of the body temperature (>37,5°C)

- shivering
- pruritus

*Expected Adverse Reaction related to local intra-discal injection*

- headache and nausea (undetermined frequency, not severe) The following adverse reactions are severe but rare
- local infection (discitis),
- reherniation in operated segments,
- exacerbation of pain, back pain, ischialgia, sciatica, pain in extremity,
- facet joint syndrome,
- meningitis,
- epidural abscess,
- arachnoiditis,
- intrathecal hematoma,
- retroperitoneal hematoma,
- cauda equina syndrome,
- acute disc herniation,
- paralysis,
- cerebrospinal fluid leak.

*Expected Adverse Reaction related to the concomitant medication*

Cf. the current Summary of Product Characteristics (SmPC) to the product.

*Expected Adverse Reaction related to MRI*

Panic attack

*Expected Adverse Reaction related to local  
anesthesia*

- Related to local anesthetic or antiseptic :

Cf. the current Summary of Product Characteristics (SmPC) to the product (1% xylocain for local anesthetic, and chlorhexidine for antiseptic)

- Related to the procedure/technique of local anesthesia:

Anesthesia failures and insufficiencies

Hematomas and arterial dissections

Infections

Neurological lesions (traumatic nerve location or intraneural injection or injected solution toxic)

Error on injected product (Ex: antiseptic, physiological saline)

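### Patients excluded for nerve compression have no stated endpoint status, while sciatica leading to surgery counts as failure, so poor outcomes can drop out of the cell arm's result

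*Protocol*

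**What the plan says.** **Section 1.7** has two adjacent rules. For a painful patient with a neurological deficit who undergoes electromyography: "In case the results obtained show pinched sciatic nerve, the investigator will decide to exclude the patients from" the trial, after which standard care follows. No responder status is given. The next rule reads: "In case of severe neuropathic pain (sciatica), the patient will be allowed to perform surgery, he will be considered as a failure".

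**Section 3.5** lists events on which patients must be withdrawn, among them "Occurrence of a SAE or an exclusion criteria, which would interfere with the patients continued participation". **Section 3.2** has as one exclusion criterion "Lumbar disc herniation and sciatica", so these conditions can trigger that rule if they arise after treatment.

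**Section 8.3** lists, among expected reactions to the intradiscal injection, "exacerbation of pain, back pain, ischialgia, sciatica, pain in extremity" and acute disc herniation, in a group described as severe but rare. **Section 5.6** says of the control arm: "No disc injection, no placebo injection will be performed in the control patients".

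**Section 3.7** requires a patient who discontinues for an AE to be followed to the last patient's last visit and until the event resolves or stabilises. For withdrawals generally it asks for the final-visit examinations as far as possible.

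**Section 7.5** leaves the imputation rules to the SAP and adds a condition: "if the missing data is type MAR (Missing At Random) or MCAR (Missing Completely At Random), a multiple imputation will be implemented". **Section 7.2** adds a worst-case sensitivity analysis that scores missing patients as non-responders in the cell arm and as responders in the control arm.

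**The concern.** Both rules in Section 1.7 concern a nerve-related deterioration in the treated region. One scores it as failure; the other removes the patient and is silent on the score. Which rule applies can turn on a management decision taken after randomisation.

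Treatment is given once, at the V0 visit (Sections 1.5 and 6.2.5). Ending participation later therefore reduces no exposure, but it can forfeit the month-24 VAS and ODI on which the primary endpoint rests (Sections 2.4.1 and 4.1). Because the listed reactions belong to a procedure that only the cell arm receives, the loss can be related to both treatment and outcome. If such patients leave the responder comparison, or enter it with an optimistic value, the difference is biased towards the cells.

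**Working it through.** **1. The plan's own figure.** Inputs from Section 7: control 30%, cells 68%, power 80%, alpha 5%, 1:1. The two-proportion formula with pooled variance is

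n = [z_α √(2·p̄(1−p̄)) + z_β √(p1(1−p1) + p2(1−p2))]² / (p2−p1)²

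with p̄ = 0.49. Two-sided: (1.96 × 0.707 + 0.842 × 0.654)² / 0.38² ≈ 26 per arm. So 26 per group is reproduced, with no allowance for failures. The stated 20% allowance fits only a one-sided calculation: 21 × 1.2 = 25.2, rounded up to 26. I use 26 per arm below.

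**2. Endpoint status under each rule.**

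| Event | Rule | Stays in the trial? | Responder status |
|---|---|---|---|
| Neurological deficit, pinched sciatic nerve | 1.7 | No, excluded | Not stated |
| Severe sciatica with surgery | 1.7 | Not stated | Failure |
| SAE or exclusion criterion that interferes with participation | 3.5 with 3.2 | No, withdrawn | Not stated |

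**3. Size of the effect.** The documents give no number of such patients. **Assumption:** k = 1 to 3 among 26 cell patients; k = 0 is also compatible with the text. Take 16 cell responders and compare counting the k as failures (16/26) with leaving them out (16/(26−k)).

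| k | Counted as failures | Left out | Rise |
|---|---|---|---|
| 1 | 16/26 = 61.5% | 16/25 = 64.0% | 2.5 points |
| 2 | 61.5% | 16/24 = 66.7% | 5.1 points |
| 3 | 61.5% | 16/23 = 69.6% | 8.0 points |

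That is about 2.5 to 3 points per patient. Imputing the k at the average rate of the remaining cell patients would give the same rates as leaving them out.

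**4. The same effect at the planned rates.** If 68% of the other cell patients respond and the k are failures, the arm's rate is 0.68 × (26−k)/26: 65.4%, 62.8% and 60.2% for k = 1, 2, 3. The planned 38-point difference becomes 35.4, 32.8 and 30.2 points, a step of 0.68/26 = 2.6 points per patient.

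**5. Can it matter for significance?** An illustration near the threshold, using Fisher's exact test (my choice; Section 7.1 names only ANOVA and the t test), with 8/26 control responders:

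- 16/26 against 8/26, failures counted: p = 0.0505
- 16/25, 16/24 and 16/23 against 8/26: p = 0.025, 0.023 and 0.010

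The example was chosen because it lies at the margin. It shows what is possible, not what is expected.

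**The case against.** **The missing-at-random reading.** A reader might infer that these patients are treated as missing at random and imputed like completers. The protocol does not say so. Section 7.5 makes multiple imputation conditional and leaves the rules to the SAP, which is not shown. Even under that assumption, imputation could use VAS and ODI recorded at months 1, 3, 6 and 12 and at withdrawal, so a patient in severe pain need not receive an average value. This part of the objection stands in full.

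**Two situations, not one.** Section 1.7 separates a compressed nerve managed with standard care from severe sciatica that goes to surgery, and leaving the trial does not logically preclude being scored a failure. This is fair: the defect is an unstated status beside a stated one, not a strict contradiction. It still leaves related outcomes inconsistently scored.

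**Follow-up exists.** Section 3.7 requires follow-up after an AE discontinuation, and Section 8.1 lists pain, disability and quality-of-life questionnaires to month 24 among the safety parameters. Month-24 data may therefore be obtained, and the events remain in the safety tables. But Section 3.7 does not name month-24 VAS or ODI, and the general rule holds only as far as possible.

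**Limited and blinded.** Section 3.5 applies only where the event interferes with participation, and the follow-up investigator is blinded. Sciatica from the underlying disease can also occur in controls, whose removal would bias the other way. That tempers the direction of the bias but does not cancel an injection risk confined to one arm.

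**The worst-case analysis covers it.** It does count these cell patients as non-responders, but only as a sensitivity analysis, and it scores every missing control as a responder. Close to the planned rates, with 3 missing per arm, 16/23 against 7/23 becomes 16/26 against 10/26 (chi-square p = 0.10); with 5 missing, 14/21 against 6/21 becomes 14/26 against 11/26 (p = 0.41). Losing significance is no fault in a worst case, but the analysis cannot isolate this particular loss or settle the primary endpoint.

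**Rarity.** Section 8.3 calls these reactions rare, and Sections 1.4 and 1.6 say much the same of nerve injury. This stands: the effect may be small or nil.

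**Conclusion.** The point holds in a limited form. The protocol scores one nerve-related deterioration as failure, excludes a related one with no endpoint status, and has a withdrawal rule that can be triggered by complications of an injection given in one arm only. The resulting loss of month-24 outcomes can favour the cell arm. What is fixed badly is the exclusion and withdrawal text itself: no analysis plan can recover month-24 values that were never collected.

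The size is about 2.5 to 3 percentage points of cell-arm response per patient left out instead of counted as a failure. This rests on 26 per arm, about 16 cell responders, and an assumed 1 to 3 such patients. The protocol gives no count and suggests few. The documents do not establish that bias will occur, nor that these patients are imputed as missing at random. They establish that nothing in the primary comparison prevents the loss.

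**What to change.** - **Separate care from data collection (Sections 1.7, 3.5, 3.7).** Clinical management stays with the investigator and is unchanged. Only withdrawal of consent or loss of contact ends data collection; every other patient has VAS and ODI at month 24. The protocol already keeps care and participation apart in Section 8.4, where an unblinded patient is not withdrawn.
- **State the endpoint status (Section 1.7).** In the primary responder analysis, patients removed for nerve compression count as non-responders in either arm, in line with Section 1.7's own rule for surgery, and are not imputed.
- **Reconcile Sections 1.7, 3.5, 3.7 and 7.5**, so that conditional multiple imputation applies only to other missing data.

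The Section 7.2 worst case can stay as it is. The cost is wording in four sections, a few questionnaires at visits already scheduled, and possibly a slightly lower cell-arm response rate.

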### **3.7 Follow up after discontinuation**

If a patient discontinues from the study for an AE, this patient must be followed up until LPLV and until resolution or stabilization of the event.

As far as possible, in case of withdrawal, the investigator will perform all examinations scheduled for the final study visit, which includes recording of AEs. In any case, the patient will be treated in accordance with standard care in the centre.

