### **3.8 Replacement of patients**

Drop-outs will not be replaced (the sample size has been increased assuming a drop-out rate of 10%).

If a patient is withdrawn from the clinical trial before injection of the cells, it will be replaced by another eligible patient.

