#### **6.2.10 Visit 5: Month 24**

- Vital signs
- Physical exploration
- Blood sampling for routine laboratory testing
- Urinalysis
- Lateral MRI, T2, quantitative
- Pain assessment of the lumbar spine by visual pain scale (VAS)
- Oswestry Disability Index in order to measure a patient's permanent functional disability, Quality of life assessment using SF-36
- Adverse event assessment
- Concomitant medication
- Instruction for wash out (NSAIDS washout of at least 2 days before this Visit, no painkillers 24h before the visit)
- Prohibition of NSAIDsa

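### Section 1.7 excludes a patient with EMG-shown sciatic compression from the trial, an outcome-triggered exclusion for which month-24 VAS and ODI are not secured, while the next sentence keeps operated sciatica as a failure

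*Protocol*

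**What the plan says.** Protocol section 1.7 gives two rules in consecutive sentences.

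- A patient who becomes painful and develops a peripheral neurological deficit has electromyography of the legs. "In case the results obtained show pinched sciatic nerve, the investigator will decide to exclude the patients from" the trial, and the patient moves to standard care (NSAID, steroid injection, rest, physiotherapy). No responder or failure status is stated.
- In severe neuropathic pain (sciatica), "the patient will be allowed to perform surgery, he will be considered as a failure".

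The other relevant places in the protocol are these.

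- **Section 3.5** makes withdrawal mandatory on "Occurrence of a SAE or an exclusion criteria, which would interfere with the patients continued participation". Sciatica with disc herniation is an exclusion criterion in section 3.2. The date and reason of any discontinuation go into the CRF.
- **Section 3.7** requires a patient who discontinues for an AE to be followed to LPLV and until the event resolves or stabilises. It adds: "As far as possible, in case of withdrawal, the investigator will perform all examinations scheduled for the final study visit". Those examinations include the VAS and ODI (section 6.2.10).
- **Section 3.8** replaces patients withdrawn before injection. For later losses, "Drop-outs will not be replaced".
- **Sections 2.4.1 and 4.1** define response on VAS or ODI at month 24 against baseline. They have no rule for excluded or operated patients.
- **Section 7.5** leaves the imputation rules to the SAP and names multiple imputation if data are MAR or MCAR.
- **Section 7.2** adds a worst-case sensitivity analysis.
- **Section 8.3** lists, among reactions to the intradiscal injection, "exacerbation of pain, back pain, ischialgia, sciatica, pain in extremity" and acute disc herniation. For the sham, section 5.6 says "The annulus will not be perforated".

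**The concern.** After the Day 0 procedure, the rule in section 1.7 removes a randomised patient because that patient has done badly. Such a patient is more likely than average to be a non-responder. The triggering event is also a recognised complication of entering the disc, which only the cell arm undergoes, so the removals may be unbalanced and would then favour cells. Compression from progression of the disease can occur in the sham arm too, so the imbalance is plausible but not certain.

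The two adjacent sentences also give related outcomes a different standing. An operated patient stays in the trial's accounting as a failure, while a patient treated conservatively for proven compression leaves it. A patient with severe sciatica and a positive EMG meets both descriptions, and the text does not say which rule prevails.

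At stake is the completeness of the month-24 primary endpoint in a trial of 26 patients per arm, where one or two patients can move a borderline result.

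**Working it through.** The protocol gives no rate for sciatic compression and no figure for this rule, so there is nothing of its own to reproduce. The check has two parts.

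**1. Does another section secure the month-24 outcome?**

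- Section 3.7, first sentence: follow-up to LPLV after discontinuation for an AE. A new deficit with nerve compression is an AE under section 8.2, so contact continues. The sentence names neither VAS nor ODI and concerns the event.
- Section 3.7, second sentence: final-visit examinations, including VAS and ODI, but at the time of withdrawal and only where possible. A value at month 4, say, is not the month-24 value.
- Section 7.5: multiple imputation under MAR or MCAR. MAR is doubtful when removal follows clinical worsening, and imputation could credit such a patient with a response. The detailed rules are left to the SAP.
- Section 7.2: the worst case counts a missing cell patient as a non-responder and a missing sham patient as a responder. It covers the direction of concern, but only as a sensitivity analysis.

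None of these fixes a status for the excluded patient or requires month-24 VAS and ODI.

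**2. How large could the effect be?**

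Inputs: n = 26 per arm (section 2.1), alpha 5%, taken as two-sided (section 7), and a true response of 30% in both arms (the control rate in section 7). The compression rate h in the cell arm is an assumption: 0.3%, 1% or 2%. The 0.3% borrows the discitis ceiling in section 5.8 (under 0.1%, taken per disc, times 3 discs). The other two are illustrative.

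Expected cases = 26h. P(at least 1) = 1 − (1 − h)^26. P(at least 2) = 1 − (1 − h)^26 − 26h(1 − h)^25.

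| h | Expected | P(≥1) | P(≥2) |
|---|---|---|---|
| 0.3% | 0.08 | 7.5% | 0.3% |
| 1% | 0.26 | 23% | 2.8% |
| 2% | 0.52 | 41% | 9.5% |

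For the chance of a false win, take a deliberately unfavourable case: every excluded patient is a non-responder and is dropped, and no sham patient is excluded. The number excluded is k ~ Bin(26, h). Retained cell patients respond with probability 0.30/(1 − h), for example 0.30/0.98 = 0.306 at h = 2%. Sham responders are Bin(26, 0.30). Sum the probability of every outcome in which the cell rate is higher and two-sided p ≤ 0.05:

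| h | Student t on 0/1 response | Pooled z |
|---|---|---|
| 0 | 2.76% | 2.76% |
| 0.3% | 2.77% | 2.80% |
| 1% | 2.80% | 2.90% |
| 2% | 2.89% | 3.05% |

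The largest rise is 2.89 − 2.76 = 0.13 points for the t test, the test named in section 7.1, and 3.05 − 2.76 = 0.29 points for the pooled z test.

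A borderline example, against 8/26 responders in sham:

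| Cell arm | Rate | t test p | Fisher p |
|---|---|---|---|
| 15/26 (none dropped) | 57.7% | 0.052 | 0.093 |
| 15/25 (one dropped) | 60.0% | 0.036 | 0.0505 |
| 15/24 (two dropped) | 62.5% | 0.024 | 0.046 |

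One dropped patient takes the t test below 0.05. Fisher's test needs two. The counts are chosen at the edge of significance, so they show what is possible rather than what is likely.

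**The case against.** The case against is substantial, and much of it stands.

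- **The SAP may settle the status.** Section 7.5 sends imputation rules there, and the SAP is not at hand. A rule counting these patients as non-responders would need only the exclusion and its reason, which section 3.5 already puts in the CRF. A reader might infer that the SAP can do nothing because the data are gone. That is too strong: it could define a status. It could not supply an observed month-24 VAS or ODI that was never taken, and whether the visits continue is a matter of conduct that the protocol decides.
- **Follow-up does not simply stop.** Section 3.7 requires follow-up to LPLV for an AE, so a reading in which the patient disappears is not supported. The gap is narrower: the efficacy measures at month 24 are not secured.
- **The two rules cover different events.** Surgery alters VAS and ODI directly, whereas a patient treated conservatively may recover and meet the response definition at month 24. Calling that patient a non-responder is an estimand choice, not a correction of an error. This stands, and it is why retention comes first in the fix.
- **The direction is already probed.** The worst case in section 7.2 is harsher on cells than a non-responder rule in both arms. This stands, but it does not govern the primary analysis.
- **The investigator deciding on exclusion is blinded** (section 3.3). That limits deliberate selection. It does not remove bias from an event that is itself related to the arm.

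**Conclusion.** The point holds, and it is minor. Section 1.7 fixes a post-randomisation, outcome-triggered exclusion next to a rule that retains a closely related outcome as a failure. No other section secures month-24 VAS and ODI for the excluded patient, and section 3.5 points the same way. The concern applies only after Day 0, since patients withdrawn earlier are replaced.

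Under the stated assumptions the false-win chance rises by at most 0.13 points (t test) or 0.29 points (pooled z). Those assumptions are rates of 0.3% to 2% that the protocol does not give, no sham exclusions, and excluded patients dropped as non-responders. Section 8.3 describes the severe injection reactions as rare, and section 1.6 describes nerve injuries as very rare.

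A reader might infer that the protocol removes these patients from the primary analysis, or that the trial's conclusion is materially biased. The documents support neither. Exclusion from the trial is not stated to be exclusion from the analysis, and the calculated effect is small even if it were.

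**What to change.** In section 1.7, replace exclusion from the trial with this: the patient moves to the standard of care already described there and stays in scheduled follow-up (VAS, ODI, MRI, AEs) to month 24 unless consent is withdrawn.

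In section 3.5, say the same for withdrawal after Day 0 because of an SAE or an exclusion criterion.

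Optionally, for consistency with the operated-sciatica rule, count these patients as non-responders in both arms in the primary analysis. The sponsor should record this as an estimand choice. It would slightly lower the responder rate in whichever arm has such events.

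The cost is a wording amendment. Care does not change, and the visits are already in the schedule.
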